**Protocol #: 20-1692**

**Project Title: Comparing Office and Home Induction for Medication Assisted Treatment for Opioid Use Disorder (HOMER)**

**Principal Investigator: [name], MSPH**

**Version Date: 8-24-2020**

**I. Hypotheses and Specific Aims:** A brief statement of the purpose of the research project. This section should include the hypotheses and specific aims being tested in the research. *Note: If you are applying for QA/QI/PE determination, you should not use terms like "hypothesis" or "research;" Instead, use the terms "aims" or "goals" and "evaluation."* (Approx. 1 paragraph)

The purpose of this study is to compare short-term stabilization and long-term maintenance treatment outcomes of home medication assisted treatment (MAT) induction to office MAT induction for patients suffering from opioid use disorder (OUD) and opioid dependence.

### Specific Aims:

1. Compare short-term stabilization and long-term maintenance treatment engagement in MAT in patients receiving home induction to those receiving office-based induction.
2. Identify clinically relevant practice and patient characteristics associated with successful long-term treatment.

### Hypotheses:

- H1. Patients using observed (office-based) MAT induction will have a greater number of days of buprenorphine treatment than patients using unobserved (home) MAT induction at nine-month follow-up.
- H2. Patients using office-based MAT induction will be more likely to take buprenorphine on  $\geq 80\%$  of the days between day 1 and day 270 than patients using home MAT induction.
- H3. Patients using office-based MAT induction will report greater improvement in quality of life, social determinants of health and social functioning over a nine-month follow-up period than patients using home induction.
- Hypotheses 1a, 2a, 3a: Intervention effects on primary outcomes (medication-taking and quality of life) will differ for patients in subpopulations of interest, defined by high executive function, shorter history of substance use, and lower substance use.

**II. Background and Significance:** Explain the background of this project so that we will understand why it is important to perform this research project. (Approx. 1 page)

The United States faces the worst drug overdose epidemic in its history. Annual deaths from opioid drug overdose now exceed the number of people dying in car accidents. A key driver of the overdose epidemic is a sharp increase in the prevalence of OUD.

Office-based Opioid Treatment (OBOT) is the primary care or ambulatory care provision of medication assisted treatment (MAT) for patients suffering opioid use disorder (OUD). MAT with buprenorphine in primary care clinics is a proven strategy to treat opioid use disorder (OUD) and is slowly becoming accessible to patients through primary care. Treating patients with buprenorphine involves an initial induction, during which patients discontinue their opioids, begin withdrawal, and receive the first few doses of buprenorphine. National guidelines for OBOT have focused on observed (office-based) induction to begin MAT. Over the years, unobserved (home) MAT inductions have also been used and shown to be safe and effective. Individually, each induction strategy is evidence-based, guideline concordant care. Most research on which the current guidelines are based examined short-term outcomes. However, OUD is a chronic condition. MAT often involves intermittent return to illicit opioid use and treatment lapses, resulting in multiple attempts to remain in long-term treatment. Important differences between the activities that occur during a home versus an office-based induction might influence short-term stabilization, long-term maintenance treatment, and quality of life outcomes. No large-scale, multi-center, randomized comparative effectiveness research has compared home versus office-based induction on long-term outcomes for patients suffering from OUD seen in primary care settings. There is currently insufficient evidence to recommend home versus office-based induction.

Acknowledging the dire need for increased access to effective treatment for OUD, patients and providers are eager to better understand if home or office-based induction in the primary care setting leads to more successful short-term stabilization and long-term maintenance treatment and patient outcomes. They also question whether certain patient characteristics, such as substance use history, executive function, and social determinants of health, are associated with better long-term outcomes in patients receiving one method versus the other.

### **III. Preliminary Studies/Progress Report:**

Medication assisted treatment (MAT) is a proven, guideline concordant strategy to treat OUD. Historically, MAT has often involved receiving daily doses of methadone at a certified addiction treatment center (methadone clinic). However, the primarily urban locations of these centers and treatment protocols present substantial barriers to access to care. Office-based opioid treatment (OBOT), such as MAT with buprenorphine in primary care clinics, is a proven strategy to treat OUD and is slowly becoming accessible to patients through primary care. MAT provided by primary care practices has the potential to greatly increase access to care, reduce preventable deaths from overdose, and improve quality of life.

Treatment with buprenorphine begins with “induction,” during which patients discontinue their opioids, begin withdrawal, and receive the first one to four doses of buprenorphine. Induction may be performed using either an office-based or home induction protocol. Both strategies are evidence-based and considered standard care. However, previous research has focused on short-term outcomes. No data are available indicating which method leads to superior long-term maintenance treatment outcomes or which option might be a better fit for certain types of patients.

MAT consists of 3 phases: induction, stabilization, and maintenance. For induction, patients discontinue their opioids, begin withdrawal, and receive the first one to four doses of buprenorphine. The neurobiology of addiction requires that a person achieve a level of withdrawal in order for buprenorphine to be effective, which requires patients take their last

opioids 24 – 72 hours prior to induction. If given too early, buprenorphine can rapidly precipitate an intense opioid withdrawal. Because of concerns about this risk, inductions have often occurred in the primary care clinic with monitoring from the clinic staff (“observed” or office-based induction). Timing the last use of opioids such that patients arrive during available office hours for induction while in withdrawal is challenging. Further, office induction is a resource intensive activity requiring space, provider and staff time, and patient effort. Based on our previous work (IT MATTTTRs), office-based induction might require one to three hours of patient time in the office, two to four staff interactions, and one to three prescriber interactions. Other care providers, including behavior health, peer counselors, and ancillary staff may have additional interactions with the patient. Busy primary care practices, rural health centers, Federally Qualified Health Centers, and other safety net clinics must balance access to onsite care for many patients with the needs of an individual patient with OUD. Some practices are reluctant to dedicate this amount of resource for one patient encounter. Although resource intense, these same office-based resources might also create a positive cumulative benefit for patients not available in-home inductions, including enhanced patient-provider-practice interaction and support for patient behavioral factors (motivation, planning, and action control) known to affect long-term adherence to treatment

Home (or “unobserved”) induction is an alternative strategy that poses fewer practice challenges and allows patients to begin buprenorphine therapy according to their schedule. For home induction, patients can stop opioids at any time and start buprenorphine when they reach the appropriate level of withdrawal. Stigma associated with OUD and difficulty with transportation may present other barriers to starting MAT at the clinic. Some patients may prefer undergoing MAT induction in the relative comfort of their own home. However, while potentially more convenient, some patients lack social supports and relationships and the cognitive ability to set goals and follow through on plans (low executive function) often necessary for successful MAT induction and treatment.

Patients typically transition into the stabilization phase of MAT 24 to 48 hours after induction. Stabilization may last one to three months. During this time, patient motivation is challenged, temptations and roadblocks may jeopardize plans made by the patient (internal plans) and plans made by the practice and family (external plans), and actions of treatment maintenance are not yet routine. Successful induction may provide a firm foundation for this difficult stabilization phase. As patients begin routine medication use, they no longer suffer withdrawal symptoms and do not engage in opioid-seeking behavior. MAT initially focuses treatment on the opioid dependence. As patients successfully maneuver through MAT stabilization, they are often able to address the behavioral factors associated with their addiction. At this point, patients enter the maintenance phase of MAT, during which they are more able to turn their attention to other elements of their life. They can address many of the social determinants of their health, such as education and employment, along with mental, emotional, and behavioral health issues. Successful induction sets the stage for successful MAT stabilization and long-term maintenance treatment.

Important differences between the activities that occur during a home versus office-based induction may influence the induction success, short-term stabilization, long-term maintenance treatment, and quality of life outcomes. A recent review identified ten studies describing home induction, with just one randomized controlled trial with 20 patients observed for up to 12 weeks. However, no large-scale, multi-center, randomized comparative effectiveness research has compared home versus office-based induction on long-term outcomes for patients

suffering from OUD receiving treatment in primary care settings. Additionally, no studies have explored whether specific types of patients are more likely to benefit from home versus office-based induction. There is currently insufficient evidence to recommend home versus office induction.

Providers and patients seek clarity about the benefits and risks of home inductions compared to office-based inductions. This comparative effectiveness study of the existing, evidence-based home induction and office-based induction strategies for MAT will examine long-term outcomes to help fill this critical evidence gap.

#### **IV. Research Methods**

##### **A. Outcome Measure(s):**

HOMER is a randomized comparative effectiveness research study to compare differences in short-term and long-term outcomes in patients who begin medication assisted treatment (MAT) for opioid dependence or opioid use disorder (OUD) with an unobserved induction (home induction) or an observed (office-based) induction. The primary outcomes are:

1. Number of days of buprenorphine treatment between day one and day 270 of treatment
2. Number of days of use of illicit opioids between day one and day 270 of treatment.
3. Percent of patients in each group who took buprenorphine on  $\geq 80\%$  of the days between day one and day 270.
4. Percent of patients in each group using illicit opioids on  $< 10\%$  days from induction to nine-month follow-up.
5. Quality of life and social functioning

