|-----------------------------------------------------------------------------------------------------------------------------------------------------------|--------------------------------------------------------------------------------------------------------------------------------------------------------------------------------------------------------------------------------------------------------------------------------|-------------------------------------------------------------------------------------------------------------------------------------------------------------------------------------------------------------------------------------------------------------------------------------------------------------------------------------------------------------------------------------------|
| Primary Outcomes                                                                                                                                   | Timing of data collection indicated by *, **, †, ‡, §, ¶                                                                                                                                                                                                                |                                                                                                                                                                                                                                                                                                                                                                                           |
| Number of days patient took buprenorphine between Day 1 and Day 270†                                                                                      | 
 
▪ Prescription refills†
 
▪ Patient self-report of number of days buprenorphine taken†
 
                                                                                                                                | 
 
▪ Practice Participant Tracker
 
                                                                                                                                                                                                                                                                                                          |

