| Patient-Centered Outcomes±                                                                                                                         |                                                                                                                                                                                                                                                                                |                                                                                                                                                                                                                                                                                                                                                                                           |
| Social Determinants of Health and Quality of Life                                                                                                         | Patient surveys completed per clinical care on quality of life (e.g., symptoms, side effects, depression), social connectedness, loneliness, and other select determinants of health**                                                                                         | 
 
▪ NIH PROMIS or SF 12 or 20
 
▪ Activity and Participation Questionnaire
 
▪ Social & Community Opportunities Profile
 
▪ UCLA 3-item Loneliness Scale
 
▪ American Academy of Family Physicians Social Determinants of Health tool
 
 |
| Patient-Level Moderators and Mediators±                                                                                                            |                                                                                                                                                                                                                                                                                |                                                                                                                                                                                                                                                                                                                                                                                           |

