##### *Quantitative Analytic Plan*

After generating initial descriptive statistics on patient and practice characteristics, we will report on differences between: (1) intervention arms and (2) patient dropouts vs. non-dropouts. We will use an intent to treat analysis to assess the effect of the interventions on long-term treatment. We will examine baseline characteristics of patients in both arms using Pearson’s  $\chi^2$  tests for categorical variables and t-tests for continuous variables to assess for unbalanced confounders. Patient engagement in treatment at 30, 90, and 270 days will be analyzed. Given that the comparators employ different strategies that might affect long-term treatment outcomes, we hypothesize that we will observe a difference in outcomes between the two induction strategies. Patient-level covariates will be screened in bivariate analyses and included in multivariate analysis if related to the outcome at  $p<.2$  or are associated with dropout. Covariates (to adjust for potential confounding) and potential moderators will include age, gender, race/ethnicity, comorbidities, and other sociodemographic and health-related variables.

In the event normality assumptions are not met, we will use transformations to normalize distributions, ordinal or Poisson regression where appropriate, and/or the appropriate link function (e.g. logit link for dichotomized measures). We will employ intent to treat analyses using general (generalized) linear mixed models (GLMMs) to incorporate hierarchical and longitudinal data structures. Hypothesis tests will be two-sided with  $\alpha = .05$  or p values reported. Goodness of fit statistics and model fitting diagnostics will be used to assess influential points, outliers, overdispersion and heteroscedasticity and to evaluate alternative model specifications. All statistical analyses will be performed using SAS version 9.4 (SAS Institute Inc., Cary, N.C.).

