Outcomes for this analysis will be scores on quality of life, social functioning, social determinants of health assessments at baseline, 30 days, 90 days, and 270 days. We will use random coefficient growth curve models to determine whether trajectories on quality of life and other patient reported measures for patients receiving home induction compared to patients receiving office-based induction (time x arm interaction term in mixed model notation).

***H1a, 2a, 3a: Intervention effects on primary outcomes (medication-taking and quality of life) will differ for patients in subpopulations of interest, defined by high executive function, shorter history of substance use, and lower substance use.***

We will conduct exploratory analyses to test for potential effect modification (moderator of intervention effectiveness) by selected patient characteristics. The general hypothesis for these moderator analyses is as follows: The effects of the home versus office-based induction on patient medication-taking (and other primary outcomes) will differ by baseline levels of executive function and substance use (amount and shorter history), dichotomized by baseline scores.

For hypotheses 1 and 2, moderator analyses involve inclusion of main effect for the moderator and a moderator x intervention term. The interaction term tests the differential effect of the intervention on the outcome for subgroups defined by the moderator variable. For hypothesis 3, moderator analyses involve inclusion of the main effects for time, arm, moderator variable, time x arm, time x moderator, arm x moderator, and time x arm x moderator interaction term in the model. The three-way interaction term tests for differential intervention effectiveness by subgroups identified by the moderator variable. Due to the exploratory nature of these analyses, we do not plan to adjust for multiple comparisons in moderator analyses using the subgroups defined above. However, interpretation of results will include reporting on all subgroup analyses and take into account the number of subgroup analyses performed.

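### The protocol contradicts itself on which outcomes are primary, ranks none first, and gives the two illicit-opioid primaries no hypothesis or analysis of their own

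*Protocol*

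**What the plan says.** Section IV.A (Outcome Measure(s)) gives five primary outcomes: days of buprenorphine treatment; "Number of days of use of illicit opioids between day one and day 270 of treatment"; buprenorphine on at least 80% of days; illicit opioids on fewer than 10% of days; and "Quality of life and social functioning".

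Table 1 (Section IV.D) puts the first four under "Primary Outcomes". Quality of life and social determinants of health come under a different heading, "Patient-Centered Outcomes", with a footnote that the choice of instruments is still open.

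Hypotheses 1a, 2a and 3a, in Section I and again in Section IV.F, read: "Intervention effects on primary outcomes (medication-taking and quality of life) will differ for patients in subpopulations of interest". Illicit opioid use is not in that parenthesis.

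The main hypotheses cover buprenorphine days (H1), the 80% threshold (H2) and patient-reported outcomes (H3: "Patients using office-based MAT induction will report greater improvement in quality of life, social determinants of health and social functioning"). The tests set out by hypothesis in Section IV.F follow the same three.

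The Quantitative Analytic Plan states: "Hypothesis tests will be two-sided with $\alpha = .05$ or p values reported". Sample Size and Power works at .05 for a dichotomous outcome (treatment retention) and for continuous outcomes such as quality of life and the share of days on buprenorphine. Section IV.F mentions secondary outcomes, but no outcome in the protocol is labelled secondary.

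**The concern.** A reader cannot tell from the protocol which result decides the trial. Quality of life is primary in one list and not in another. Illicit opioid use is primary in both lists but has no directional hypothesis and no model of its own. Nothing is ranked first.

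A claim that one induction method is better could therefore rest on any of several outcomes, and the status of an outcome would depend on which section is cited. If several outcomes are each tested at .05 and any one is enough, the trial-level error rate exceeds 5%. This matters because the protocol presents the trial as filling an evidence gap on long-term outcomes of the two methods.

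**Working it through.** **Step 1. The places side by side.**

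| Outcome | Section IV.A | Table 1 | Parenthesis in H1a-3a | Hypothesis and specific model |
|---|---|---|---|---|
| Buprenorphine days | primary | primary | covered (medication-taking) | H1 |
| Illicit-opioid days | primary | primary | not named | none |
| Buprenorphine on at least 80% of days | primary | primary | covered (medication-taking) | H2 |
| Illicit opioids on under 10% of days | primary | primary | not named | none |
| Quality of life / social functioning | primary | separate block | quality of life named | H3 |

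Only the two buprenorphine outcomes have the same status everywhere. The illicit-opioid outcomes are reached only by the general statement in Section IV.F that mixed models will be used for primary and secondary outcomes.

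**Step 2. The plan's own power figures (two-sided .05, 1:1).** They reproduce.
- 45% vs 54%, 500 per arm. The standard error under the null is sqrt(2 × .495 × .505 / 500) = .03162, and under the alternative sqrt((.45 × .55 + .54 × .46) / 500) = .03149. Power = Φ((.09 − 1.96 × .03162) / .03149) = Φ(.890) = 81.3%.
- .18 SD, 500 per arm: Φ(.18 × sqrt(250) − 1.96) = Φ(.886) = 81.2%.
- .20 SD, 400 per arm: Φ(.20 × sqrt(200) − 1.96) = Φ(.868) = 80.7%.

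The sample-size arithmetic is not in error.

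**Step 3. Illustration of the error rate.** Suppose k primaries are each tested at .05 and any one supports a claim. The three values of k are H1-H3 (3), Table 1 (4) and Section IV.A (5). Under independence the chance of at least one false positive is 1 − .95^k. Under correlation it was simulated with 1,000,000 draws of correlated normal test statistics. All correlations are assumptions.

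| k | Independent | Common .3 | Common .5 | Common .8 | Mixed pattern |
|---|---|---|---|---|---|
| 3 | 14.3% | 13.6% | 12.5% | 9.8% | 12.1% |
| 4 | 18.5% | 17.4% | 15.6% | 11.4% | 13.8% |
| 5 | 22.6% | 20.9% | 18.3% | 12.7% | 17.6% |

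The mixed pattern takes .8 between a day count and its own threshold, .5 between buprenorphine and opioid measures, and .3 with quality of life. Each threshold outcome is a cut of a day count, so strong correlation within those pairs is plausible. The range of 10-18% covers the mixed pattern and common correlations of .5 to .8. A uniform .3 across five tests would give 21%.

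**Step 4. Power under an equal split of alpha.** Over five primaries (.01 each), power for 45% vs 54% is Φ((.09 − 2.576 × .03162) / .03149) = 60.7%. Keeping 81% would need about 735 per arm. With one lead outcome at .05, the stated 81% stands.

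**The case against.** Several points limit how far this goes.

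- **Multiplicity rules usually belong in the statistical analysis plan**, which is not at hand. This stands: the absence of an alpha allocation in the protocol is not itself a finding. The conflicting lists remain, because such a rule needs one agreed list to act on.
- **The moderator parenthesis is not a full third list.** A reader might infer three rival definitions. But the wording sits in moderator versions of H1-H3, and the text below it in Section IV.F refers to medication-taking and other primary outcomes. The clear conflict is between Section IV.A and Table 1, over quality of life. The parenthesis adds ambiguity.
- **Testing every primary at .05 is not quite what is written.** The sentence allows p values to be reported instead, and the power section does not mention illicit opioid use. This stands, and the error rates are conditional for that reason.
- **A reader might infer an error rate of 23%, or well above it.** The 22.6% figure needs five independent tests, which cannot hold for a count and its own cut-off. Counting five quality-of-life tools as separate tests would make nine tests, and 1 − .95^9 = 37%. But Table 1 calls the tools potential, offers some as alternatives and leaves the selection open, so the documents do not support that count.

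**Conclusion.** The concern holds as a contradiction within the protocol. Quality of life is primary in Section IV.A but not under the primary heading of Table 1. The moderator hypotheses describe the primaries without naming illicit opioid use. Two listed primaries have no hypothesis and no outcome-specific analysis, and there is no lead outcome. None of this depends on an unseen document.

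The size is illustrative only: about 10-18% for at least one false positive under the assumed correlations, and 14-23% under independence. Both ranges assume that three to five primaries are each tested at .05 and that any one is enough for a claim. Even the low end is about twice 5%.

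**What to change.** Use one primary list in the Hypotheses section, Section IV.A, Table 1 and the moderator section of IV.F.

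- **Name one lead primary at two-sided .05.** Buprenorphine days (H1) is the natural candidate: it is primary in every place, has a hypothesis and a model, and keeps the stated 81% power.
- **Label the other outcomes secondary**, or control error across any that stay co-primary by a method that the sponsor chooses. A fixed order is one option.
- **Give the illicit-opioid outcomes a hypothesis and a model**, or relabel them as secondary.
- **Keep the planned time-by-arm growth-curve analysis for quality of life**, on one named instrument if it stays primary.

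The cost is protocol wording, with no added patients. Non-lead outcomes carry weaker claims. In a fixed order of five tests, each with 81% power and assumed independent, the last would be reached and won only .81^5 = 35% of the time; positive correlation raises this. An equal split instead lowers power to about 61% for each of five tests.
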